**Figure 1 figure1:**
[figure not shown]
Intervention districts in Nampula Province, Mozambique.

Conducting a cluster randomized controlled trial (cRCT) through passive surveillance to establish confirmed malaria cases among participating children.Conducting a prospective chemoprevention efficacy cohort study to determine whether SP+AQ provides 28 days of protection from infection, and whether drug concentrations and resistance influence the duration of protection.Conducting a resistance marker study in children aged 3 to 59 months in the two research districts plus the two standard intervention districts to describe changes in resistance marker prevalence over time.Conducting a process evaluation of the SMC implementation looking at cost and process outcomes.

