**Methods:**

This type 2, hybrid, effectiveness-implementation study uses a convergent mixed methods approach. SMC will be implemented in four monthly cycles between December 2021 and March 2022 in four districts of Nampula Province. Phase 2 will include four components: (1) a cluster randomized controlled trial to establish confirmed malaria cases, (2) a prospective cohort to determine the chemoprevention efficacy of the antimalarials used for SMC and whether drug concentrations or resistance influence the duration of protection, (3) a resistance marker study in children aged 3 to 59 months to describe changes in resistance marker prevalence over time, and (4) a process evaluation to determine feasibility and acceptability of SMC.

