### Objectives

Phase 2 aims to test the feasibility, effectiveness, and chemoprevention efficacy of SMC with SP plus AQ (SP+AQ) in Nampula Province in Mozambique, where malaria transmission is highly seasonal. Specific objectives include the following:

To determine the effectiveness of SMC in reducing the incidence of malaria infection among children aged 3 to 59 months.To determine and measure efficacy as follows:To determine chemoprevention efficacy of SP+AQ when used for SMC in Nampula Province, Mozambique.To calculate the extent to which efficacy is impacted by drug resistance and drug concentrations.To investigate the presence and change of SP+AQ– and piperaquine-resistance markers over time as a result of SMC implementation.To understand the impact of the SMC implementation model by determining process, costing, and acceptability outcomes for the intervention.

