#### Chemoprevention Efficacy Study

The primary outcome is chemoprevention failure in the presence of adequate drug concentration and associated parasite genotype, as defined by quantitative polymerase chain reaction (qPCR)–positive parasites on day 28 or a positive malaria slide at any time from day 7. Secondary outcomes include uncomplicated malaria within the first 28 days, hospitalization within the first 28 days, and severe malaria within the first 28 days.

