#### Chemoprevention Efficacy Cohort Study

This component will investigate the chemoprevention efficacy of SP+AQ at current dosing regimens among SMC-eligible children. Following the WHO’s Malaria Chemoprevention Efficacy Study Protocol [30], both malaria thick smears and dried blood spots (DBSs) will be taken at day 0, day 2, day 7, day 14, day 21, and day 28 during and after administration of the first cycle of SP+AQ, which will be administered through directly observed therapy. All DBS samples on day 0 and day 28 will be processed to ascertain low-density parasitemia estimates through qPCR. If sufficient DNA exists, day-0 and day-28 samples will be genotyped and compared. If children are found to have the same haplotype, this will indicate a recrudescent infection. If different haplotypes are present or if there is presence of an infection on day 28 that was not present on day 0, this will indicate a new infection after SP+AQ administration. Day-7 samples will also be processed for drug levels of all three SMC drugs, and day-28 samples will be processed for SP and AQ. The qPCR methodology is primed to detect presymptomatic parasitemia of clinical relevance. More sensitive PCR methodologies will not be conducted in order to prevent detection of extremely low–level parasitemia that will not be of clinical significance. DBSs will also be processed for estimates of blood parasite density and genotyping of relevant drug-resistance markers on days 2, 7, 14, and 21 if a child’s thick smear on those days was positive or if DBSs at a later time point are *P falciparum* positive. A DBS will also be collected whenever a child has a fever and is positive on a malaria RDT based on histidine-rich protein 2 and plasmodium lactate dehydrogenase. Drug level, qPCR parasite estimation, and genotyping will also take place. A blood smear will not be taken, as the RDT diagnosis will be sufficient when associated with fever. An RDT will not be given to children on day 0 unless they have signs and symptoms of malaria as per the standard SMC protocol, in which case they will be excluded from the study sample (see Figure 2 for an illustration of the proposed sample collection time points and subsequent sample processing sequence). We aim to recruit participants from within Lalaua, one of the new phase 2 research districts.

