#### Chemoprevention Efficacy Cohort Study

Distributions and proportions of relevant mutations will be analyzed to compare the chemoprevention efficacy between groups of mutations. The blood drug concentrations will be analyzed as a cohort by mean, median, and SD, and statistical tests of their associations with treatment outcome—in particular, drug concentrations on day 7—will be performed. The focus will be on outliers with low levels of drug concentration based on the outcome measures described. Day-28 positivity will be associated with antimalarial drug resistance genotype.

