In phase 2 of the study, more work is needed to understand the efficacy of SP+AQ to clear existing infections and prevent new infections. This is what we mean by the term “chemoprevention efficacy.” The phase 2 chemoprevention cohort will determine whether SP and AQ in combination using current dosing regimens for SMC-eligible children are able to prevent infections over a 28- to 31-day period between cycles during the high-transmission season. Importantly, this cohort will also determine whether these drugs can also clear asymptomatic malaria to provide an estimate of chemoprevention efficacy in terms of prevention of both new and recrudescent infections. This will help determine the duration of effectiveness of SP+AQ. Further work is also crucially needed to map antimalarial drug resistance in these key populations in Mozambique, which has already been frequently highlighted in the literature [32]. The relationship between chemoprevention effectiveness and chemoprevention efficacy and how it relates to drug resistance is currently unclear. The chemoprevention efficacy component of this study aims to elucidate that relationship within the context of Northern Mozambique. The intention is to create a system where the relationship between these variables is better understood within and across malaria ecologies. We may find that drug resistance across Northern Mozambique and how it relates to effectiveness and efficacy covers a large geographical area, but this must be confirmed through future work once we better understand the dynamics of these interactions. Therefore, in the process of validating this methodology and analyzing these dynamics, it is prudent to create a geographical restriction to the assumptions of this protocol, whereby resistance to SP, in particular, may be representative of a given parasite population [13].

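### The chemoprevention cohort is asked about duration of protection, but its outcome is binary failure by day 28, no time-based measure is stated, and the genotype analysis uses a narrower event than that outcome

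*Protocol article*

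**What the plan says.** **Aim.** The component list under Methods, Study Design has the cohort test for 28 days of protection and "whether drug concentrations and resistance influence the duration of protection". The Abstract (Methods) repeats this as "whether drug concentrations or resistance influence the duration of protection". The numbered objective under Objectives is worded without duration: "To calculate the extent to which efficacy is impacted by drug resistance and drug concentrations". The Discussion (Principal Findings) says the cohort will help establish how long SP+AQ works, and speaks of the drugs' ability to "prevent infections over a 28- to 31-day period between cycles".

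**Outcome.** Under Primary and Secondary Outcomes, Chemoprevention Efficacy Study, failure means qPCR-positive "parasites on day 28 or a positive malaria slide at any time from day 7". The secondary outcomes are also yes/no: "uncomplicated malaria within the first 28 days, hospitalization within the first 28 days, and severe malaria within the first 28 days".

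**Sampling.** Under Recruitment and Data Collection, smears and dried blood spots (DBS) are taken on days 0, 2, 7, 14, 21 and 28. qPCR is unconditional on days 0 and 28 only. DBS from days 2 to 21 are processed if that day's smear "was positive or if DBSs at a later time point are" positive for *P falciparum*.

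**Analysis.** Under Data Analysis, Chemoprevention Efficacy Cohort Study, efficacy is compared between mutation groups, and drug concentrations (chiefly day 7) are tested against treatment outcome. The section ends: "Day-28 positivity will be associated with antimalarial drug resistance genotype".

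**The concern.** There are two mismatches.

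First, a question about duration needs a quantity that depends on time. Neither the outcome nor the analysis supplies one, so two cohorts with the same failure proportion but very different times to infection would give the same result.

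Second, the sentence on resistance genotype does not use the cohort's own failure definition. Positive slides from day 7 count as failure in the outcome, but an early failure who is negative on day 28 would sit with the successes in the genotype analysis. Such a child had among the shortest protection, and the DBS from the slide-positive day is due to be genotyped, so resistance data would exist and go unused. If resistance shortens protection, putting such children among the negatives would tend to weaken the association being sought.

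**Working it through.** **1. The plan's own figure.** Inputs from Sample Sizes, Chemoprevention Efficacy Cohort Study: 3% breakthrough, n = 494, stated 95% CI 1.7% to 4.9%.
- Expected failures: 0.03 × 494 = 14.82, about 15.
- Exact (Clopper-Pearson) interval at 14.82 events: 1.68% to 4.91%, which rounds to the stated interval.

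The arithmetic is sound. It sizes the cohort for one binary proportion.

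**2. What a binary outcome cannot show.** Suppose all 15 failures begin at day 10.5, or all at day 24.5 (illustrative midpoints of days 7–14 and 21–28). The failure proportion is 3% in both cases.
- Infection-free time per failing child differs by 24.5 − 10.5 = 14 days.
- Mean infection-free time to day 28 over the whole cohort is 28 − 0.03 × (28 − 10.5) = 27.475 days against 28 − 0.03 × (28 − 24.5) = 27.895 days, a difference of 0.42 days. It is small because so few children are expected to fail.

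**3. Outcome and genotype sentence side by side.**

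| Child | Outcome section | Genotype sentence |
|---|---|---|
| qPCR-positive on day 28 | failure | positive |
| Slide-positive on day 14, negative on day 28 | failure | negative |
| Never positive | success | negative |

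The middle row is the conflict. If k of the 15 expected failures fall there, k/15 of the events change side; one child is 1/15 = 6.7%. The documents give no value for k.

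**4. Whether the planned samples can date infection.** A day-28 positive triggers processing of that child's earlier DBS. First detection is then bracketed by adjacent visits (7–14, 14–21 or 21–28), an interval of 7 days, instead of 28 − 7 = 21 days if only days 7 and 28 were read. Slide-positive children are dated by their smears. Interval-censored dating to about a week is therefore feasible in children found positive.

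**5. What 15 events would support.** Schoenfeld's approximation, two-sided alpha 0.05. The split of children between a low and a high group is an assumption, because the article gives none. With d events and fraction p in one group:
- smallest HR at 80% power = exp[(1.960 + 0.842) / √(d·p·(1 − p))]
- p = 0.5: exp(2.802 / √3.75) = 4.2
- p = 0.25: exp(2.802 / √2.8125) = 5.3

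| Split | Power, HR 2 | Power, HR 3 | Events for 80% power at HR 2 |
|---|---|---|---|
| 50:50 | 27% | 57% | 66 |
| 25:75 | 21% | 45% | 88 |

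**The case against.** **A condensed article.** The cohort analysis is a short paragraph, and a fuller protocol or analysis plan may contain a time-to-event model. The numbered objective speaks of efficacy, which failure by day 28 can answer. This has weight for the missing model. It does not cover the genotype sentence, which is a stated rule that disagrees with the stated outcome. The same article also names Cox models, first-event and recurrent-event versions, and censoring for the cluster trial.

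**Day 28 only.** A reader might infer that the whole cohort analysis looks at day 28 alone. It does not: the outcome counts slides from day 7, drug concentrations are tested against treatment outcome, and the comparison between mutation groups is not tied to day 28. Only the genotype sentence is.

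**A large, known loss of events.** A reader might also infer that early slide-positive children are treated, turn negative by day 28, and make up a substantial share of failures. The article does not say what follows a positive slide in this cohort and gives no early share. Neither the number affected nor the size of any bias can be derived.

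**Undatable day-28 positives.** A low-density infection starting around day 12 might seem bound to be recorded as a day-28 event. The processing of earlier DBS largely answers this.

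**Limits of a time analysis.** These objections stand. Smear-negative infections that clear before day 28 are never seen, because day 2–21 DBS are read conditionally. An early positive may be an uncleared day-0 infection rather than a new one. Infecting genotype is unknown in children who stay uninfected, so duration by infecting genotype cannot be estimated for them.

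**Conclusion.** The point holds in two parts. The stated aim concerns duration, while the outcome is binary failure by day 28 and no time-to-infection measure is stated. In addition, the genotype analysis uses a narrower event than the primary outcome, so the same child can be a failure in one and a negative in the other.

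The second part follows from the text without any assumption, but its numerical effect is unknown. The first part allows that an unseen document may add a model; as the article stands, its aim and its analysis do not match. The expected 15 failures rest on the plan's 3% assumption, and the detectable hazard ratios of 4.2 to 5.3 also rest on the assumed group splits. A time analysis would therefore describe duration and could not reliably test moderate effects.

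A smaller matter is the 28- to 31-day wording in the Discussion, which goes past the last scheduled sample on day 28. The design section claims only 28 days.

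**What to change.** 1. In Data Analysis, Chemoprevention Efficacy Cohort Study, replace day-28 positivity in the genotype sentence with chemoprevention failure as defined under Primary and Secondary Outcomes.
2. Choose one of the following:
   - Add time from day 0 to the first *P falciparum*-positive slide or DBS from day 7 onward, interval-censored between visits and using the DBS processing already planned. Relate it to day-7 drug concentration, report an estimate with its confidence interval, and keep recrudescent and new infections separate where genotyping allows.
   - Restate the aim in the Abstract and Study Design as association of drug concentration and resistance with failure by day 28.
3. Limit the protection claim in the Discussion to 28 days.

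The cost is analysis wording and, under the first option, one model; no extra samples are needed. If the first option is chosen, state its limits beside it: imprecision with about 15 events, unseen smear-negative infections that clear before day 28, and no estimate of duration by infecting genotype in uninfected children.

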### Study Setting

Individual elements of the study will be conducted in all four districts. The cRCT and process evaluation will be conducted in Lalaua and Muecate districts in Nampula Province, Northeastern Mozambique (Figure 1). The chemoprevention efficacy cohort study will be conducted in communities within the catchment area of one health facility in Lalaua district. The resistance marker study will be conducted in all four districts. As part of the process evaluation, several key informant interviews may be conducted with stakeholders who are based in Maputo.

To identify suitable districts for SMC implementation, a suitability ranking was conducted in-country with oversight from the WHO for all provinces. Criteria included a variety of factors: (1) seasonality eligible for SMC (ie, 60% of rainfall concentrated into 4 months), (2) mortality (ie, areas of highest mortality in children younger than 5 years using HMIS data), (3) access to care (ie, highest ranking given to areas where access to care was lowest), and (4) treatment-seeking behavior (ie, highest ranking given to areas where treatment-seeking behavior was lowest). The average category score was used to determine a final ranking and identify the top 20 suitable districts for maximizing the impact of SMC. From the list of suitable districts, additional consideration was given based on the importance of implementing the intervention in an area where no other new interventions were taking place so that effects could be attributable to only the intervention under investigation. Districts in Nampula Province were selected, as no indoor residual spraying or new long-lasting insecticide-treated net distribution campaigns had been targeted to these areas, allowing for a more robust attribution of SMC impact on malaria. 

### Study Population

The study population that is eligible to receive SMC includes afebrile children [1] of either gender (ie, children with a fever on the day of SMC administration will be excluded and referred to the health facility for further evaluation), aged 3 to 59 months for any of the SMC cycles, and residing in any of the four districts. Children must be 59 months or younger at the start of the first cycle; if they turn 5 years old during the SMC season, they may continue to receive SMC. If children are 2 months old or younger at the first cycle month, they can begin SMC once they are 3 months old in any cycle. During phase 1, when only Mecubúri and Malema districts were included, population data were retrieved from the National Census 2017, adjusting by an annual growth factor of 3.5% in Nampula Province, as calculated by the National Institute of Statistics. For phase 2, population figures for Mecubúri and Malema were obtained through the administrative coverage data of SMC from phase 1. For the two new districts, Lalaua and Muecate, as it was done for districts in phase 1, population figures were retrieved from the 2017 census data, projected for 2021 and considering a growth rate of 3.5% per year (Table 1). Additionally, health workers involved in SMC implementation; caregivers of children younger than 10 years of age; community leaders and key stakeholders, such as health officials at different levels of the health system; and those involved in SMC implementation will be sampled to provide information with regard to the intervention, according to the different study elements.

**Table 1 table1:** Estimated target population of seasonal malaria chemoprevention (SMC) districts.

District	Population^a^ for each eligible children’s group by age, n		
	3-11 months	12-59 months	All children
Malema	8500	35,800	44,300
Mecubúri	7300	36,000	43,300
Lalaua	3200	13,600	16,800
Muecate	1900	8000	9900
All districts	20,900	93,400	114,300

^a^District populations were determined by the National Institute of Statistics and SMC 2021 coverage data.

### Ethical Considerations

Ethical approval for this study was received from the Comité Nacional de Bioética para a Saùde (CNBS) of the Mozambique Ministry of Health on December 22, 2021 (reference No. 803/CNBS/21), and by the Research Ethics Committee of the Hospital Clinic of Barcelona on December 20, 2021 (reference No. HCB/2021/0944). Only participants who meet the inclusion criteria and whose caregivers provide written informed consent will be included in the study. The trial has been registered at ClinicalTrials.gov (NCT05186363).

### Primary and Secondary Outcomes

The primary outcomes for the different elements are presented below by component.

#### Cluster Randomized Controlled Trial

The primary outcome for this component of the protocol is the incidence of confirmed malaria cases using a rapid diagnostic test (RDT) reported through passive surveillance. Secondary outcomes include severe anemia, as an indication of severe malaria, and parasitemia levels, both gametocyte carriage rates and density of *Plasmodium falciparum* trophozoites and *P Falciparum* gametocytes.

#### Chemoprevention Efficacy Study

The primary outcome is chemoprevention failure in the presence of adequate drug concentration and associated parasite genotype, as defined by quantitative polymerase chain reaction (qPCR)–positive parasites on day 28 or a positive malaria slide at any time from day 7. Secondary outcomes include uncomplicated malaria within the first 28 days, hospitalization within the first 28 days, and severe malaria within the first 28 days.

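### The cohort's primary failure definition has no limb for a febrile, RDT-positive episode, and no slide is taken at such a visit, so some clinical breakthroughs can meet neither criterion for failure

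*Protocol article*

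**What the plan says.** All references are to the Protocol article.

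- **Primary and Secondary Outcomes, Chemoprevention Efficacy Study.** The outcome carries a qualifier: "The primary outcome is chemoprevention failure in the presence of adequate drug concentration and associated parasite genotype". Failure itself has two limbs, qPCR-"positive parasites on day 28 or a positive malaria slide at any time from day 7". Clinical malaria comes in at the next level: "Secondary outcomes include uncomplicated malaria within the first 28 days".
- **Recruitment and Data Collection, Chemoprevention Efficacy Cohort Study.** Thick smears and dried blood spots (DBS) "will be taken at day 0, day 2, day 7, day 14, day 21, and day 28". Routine qPCR is confined to two days: "All DBS samples on day 0 and day 28 will be processed to ascertain low-density parasitemia estimates through qPCR". For clinical episodes, "A DBS will also be collected whenever a child has a fever and is positive on a malaria RDT", and for that visit "Drug level, qPCR parasite estimation, and genotyping will also take place". The next sentence removes the slide: "A blood smear will not be taken, as the RDT diagnosis will be sufficient when associated with fever".
- **Sample Sizes, Chemoprevention Efficacy Cohort Study.** The cohort is sized for precision: a 3% breakthrough infection rate in 494 children, with a 95% CI of 1.7% to 4.9%.
- **Data Analysis, Chemoprevention Efficacy Cohort Study.** Day-28 positivity is to be related to resistance genotype. Drug concentrations, day 7 in particular, are to be related to treatment outcome.

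**The concern.** The two sections treat the same event differently. Data collection accepts fever plus a positive RDT as enough to diagnose malaria and therefore takes no slide. The primary outcome gives fever plus RDT no weight and, apart from qPCR on day 28, recognises only a slide. At the visit where a clinical breakthrough is diagnosed, the one test that could register it as a primary failure before day 28 is not done. The qPCR that is done there falls on the wrong day to count.

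Two things are at stake. One is the failure rate for which the cohort is sized, where few events are expected and each one matters. The other is the objective of relating efficacy to resistance: an episode no longer detectable by day 28 has a genotype from its own visit but no place in an analysis built on day-28 positivity.

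**Working it through.** **Step 1. Does a gap exist on the text?** Take a child with a negative slide on day 7, fever and a positive RDT on day 10, negative slides on days 14, 21 and 28, and negative qPCR on day 28.

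| Evidence on this child | Collected? | Meets a primary limb? |
|---|---|---|
| Slide at the day-10 visit | No, by rule | Cannot |
| RDT at the day-10 visit | Yes, positive | No, RDT is not a limb |
| qPCR on the day-10 DBS | Yes | No, only day-28 qPCR counts |
| Slides on days 7, 14, 21, 28 | Yes, negative | No |
| qPCR on day 28 | Yes, negative | No |
| Uncomplicated malaria within 28 days | Yes | Secondary outcome only |

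The child meets neither limb. I assume that a scheduled slide still goes ahead when a fever falls on a scheduled day, so the gap is limited to episodes between visits. It also requires that every scheduled slide from day 7 and the day-28 qPCR be negative.

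**Step 2. Reproduce the plan's own figure.** Inputs from Sample Sizes: n = 494, rate 3%.

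- Expected failures: 494 × 0.03 = 14.82, about 15.
- Exact (Clopper-Pearson) 95% interval with x = 14.82: lower limit = beta quantile 0.025 with parameters (x, n − x + 1) = 1.68%; upper limit = beta quantile 0.975 with parameters (x + 1, n − x) = 4.91%.

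This rounds to the stated 1.7% to 4.9%.

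**Step 3. Effect of one missed case.** 1/494 = 0.20 percentage points.

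**Step 4. Illustrative range.** Let f be the share of true failures that are missed by *both* limbs. This is narrower than the share that present with fever, because scheduled slides and day-28 qPCR recover some of those. The article does not give f; the values below are assumptions. The 3% is taken as the true primary failure rate, and the drug-concentration and genotype qualifier is left aside.

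- If missed children stay in as non-failures, the recorded rate is 14.82 × (1 − f) / 494.
- If they are dropped, it is 14.82 × (1 − f) / (494 − 14.82 × f).

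| f (assumed) | Failures recorded | Kept as non-failures | Dropped |
|---|---|---|---|
| 10% | 13.3 | 2.70% | 13.34/492.52 = 2.71% |
| 25% | 11.1 | 2.25% | 11.12/490.30 = 2.27% |
| 50% | 7.4 | 1.50% | 7.41/486.59 = 1.52% |

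Excluding the children therefore does not remove the bias. At f = 50%, rounding to 7 recorded failures in 494, the exact 95% interval is 0.57% to 2.90%, which would exclude the assumed true 3%.

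**The case against.** The other side has four fair arguments.

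- **The text may intend RDT plus fever to stand in for the slide.** Calling the RDT diagnosis sufficient points that way. This stands as a likely intention, but the printed primary definition does not carry it over, and an analyst following that definition would not count the episode.
- **Scheduled sampling will catch some of these children.** True. Slides on days 7, 14, 21 and 28 and the day-28 qPCR narrow the gap. They do not close it, as the example in the working shows.
- **The events are still reported.** They are, as secondary uncomplicated malaria. That does not correct the primary rate.
- **The article condenses a fuller protocol and follows a WHO cohort protocol, neither of which is shown.** Rules for classifying unscheduled episodes may be there. This limits certainty about the governing plan. But both the outcome definition and the no-slide rule are printed here, and they do not fit together.

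A reader might infer more: that every febrile, RDT-positive child is scored as protected, that efficacy is therefore overstated by a known amount, and that these children also leave the drug-concentration analysis. The article does not support any of this. It never says how such a child is classified. It gives neither the share of failures presenting with fever nor the share missed, and its cohort sections do not describe treatment of these episodes, so clearance before day 28 is a possibility rather than a stated course. The drug-concentration analysis refers to the described outcome measures generally, which can include the secondary ones. Only the day-28 genotype association clearly leaves these cases out.

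**Conclusion.** The concern holds in a limited form. The primary definition and the no-slide rule, both followed literally, leave a class of clinical breakthrough infections that meet neither limb of failure. Their classification is not stated. If they are counted as non-failures or dropped, the error goes one way: the failure rate reads too low.

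The size is not known from the article. What can be said is that about 15 failures are expected, so each missed case costs about 0.2 percentage points, and that an assumed 10% to 50% missed would turn 3% into about 2.7% to 1.5%. Only towards the upper end of that range does the recorded rate fall below the planned lower limit of 1.7%, and nothing in the article shows that end to be likely. The range assumes that the planned 3% is the true primary failure rate and leaves the drug-concentration and genotype qualifier aside.

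It deserves correction before analysis because it affects a primary outcome with few expected events and the information needed is already planned.

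**What to change.** Reconcile the outcome definition with the cohort's data collection section by adding a third limb to primary failure: fever with a positive RDT from day 7, confirmed as *P falciparum* by qPCR on the DBS collected at that visit. The qPCR confirmation guards against a false-positive RDT. Then state that:

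1. such a child counts as failed whatever the day-28 result;
2. the qualifier on adequate drug concentration and parasite genotype applies as it does to other failures, using the drug level and genotype already planned for that visit;
3. these cases enter both the genotype analysis, which would then no longer rest on day-28 positivity alone, and the drug-concentration analysis.

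The cost is one clause in the outcome definition and matching wording in the analysis section. The DBS, qPCR, drug level and genotyping are already planned for these visits, so no new samples or assays are needed and clinical management of the children is unaffected.
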